### Sample size estimation

Participant sample size estimates were calculated for the primary outcome of retention in care 12 months after enrollment. Sample size estimates were determined for a non-inferiority test for the difference in two proportions in a cluster-randomized design, using PASS® v.14 software. Participant enrollment numbers are assumed to be equal at each cluster. The probability of participant retention 12 months after study enrollment in the control group is assumed to be 95%, derived from the relative difference in reported retention between 12 and 24 months of ART in Zimbabwe [17]. The probability of retention in the intervention arms after 12 months is also assumed to be 95%. An intracluster correlation coefficient of 0.01 for retention amongst stable ART patients associated with the same healthcare facility is assumed [26]. The non-inferiority margin is prespecified as − 3.25% (risk difference). Assuming *α* = 0.05, power of 85%, and using the one-sided Z-test (unpooled) statistic, 192 participants will be required to be enrolled per facility, with 1920 participants per arm and a total sample size of 5760 enrolled participants. As retention in care is the primary outcome, no adjustment for LTFU is made. Assuming that 75% of those on ART at a healthcare facility will be stable [17] and that 60% of these will consent to be enrolled, to reach the required sample size per facility, selected facilities require at least 430 adults currently receiving ART.

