### Data analysis plan

#### Quantitative patient-level data analysis

Descriptive measures of the study population at baseline in each study arm will be conducted using medians and interquartile ranges for continuous variables and proportions for categorical variables, to assess potential imbalances between the arms.

Individual-level outcome analyses will be conducted by intention-to-treat. For the primary outcome of patient retention, risk differences between arms will be estimated using binomial population-averaged generalized estimating equations using an identity link and an exchangeable correlation structure, specifying for clustering by facility. A small cluster size variance correction will be used, and randomization strata will be included in the model as a fixed-effect parameter. If the lower bound of the 95% confidence interval for the risk difference in patient retention of the intervention vs. control arm is greater than the non-inferiority limit of − 3.25%, the intervention will be considered non-inferior to the control. Where there are imbalances between study arms in baseline variables, these will be adjusted for in multivariable analyses.

For the outcome of viral suppression, log-binomial regression with generalized estimating equations will be used to estimate risk ratios between the study arms, specifying for clustering by facility. An exchangeable correlation structure will be used and a small cluster size variance correction applied. Viral-load suppression analyses will be conducted according to: (1) an intention-to-treat principle including all enrolled participants in the arm to which they were originally allocated and irrespective of whether they had available follow-up viral-load results or completed the study and (2) a per-protocol analysis including only patients with available viral-load results. If there are imbalances between study arms in baseline variables, these will be adjusted for in multivariable analyses. Subgroup analyses will include comparing outcomes by strata of urban or rural facility and by gender. A pooled analysis of both intervention arms vs. control will also be performed.

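### The stated 85% power holds for a one-sided 5% test, but non-inferiority is judged on a 95% confidence interval, under which the same inputs give about 77% per comparison

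*Protocol article*

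**What the plan says.** Two parts of the protocol article fix the error level for the primary comparison.

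- **Sample size estimation** takes alpha as 0.05 and power as 85% and, "using the one-sided Z-test (unpooled) statistic, 192 participants will be required to be enrolled per facility", which makes 1920 per arm and 5760 in total. Retention at 12 months is taken as 95% in the control arm and in the intervention arms, with "An intracluster correlation coefficient of 0.01 for retention amongst stable ART patients" and a margin of -3.25 percentage points.
- **Quantitative patient-level data analysis** gives the decision rule: "If the lower bound of the 95% confidence interval for the risk difference in patient retention" must be above -3.25% for an intervention to be called non-inferior to control. The estimate comes from a generalized estimating equations model with facility as the cluster and randomization strata as a fixed effect. On the variance, the section says: "A small cluster size variance correction will be used".

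The article does not say how the two levels relate.

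**The concern.** A one-sided Z-test at 5% uses a critical value of 1.645. Requiring the lower limit of a two-sided 95% interval to clear the margin uses 1.960. The sample size was therefore worked out for an easier test than the one to be applied, and the quoted power does not belong to the stated decision rule.

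Two things follow. First, an inconclusive result would be read against 85% power that the trial does not have under its own rule. Second, while both levels stand in the document, a result that clears a 90% interval but not a 95% interval can be argued either way once it is known.

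**Working it through.** **Inputs**, all from the protocol article: retention p = 0.95 in both arms, intracluster correlation 0.01, m = 192 per facility, margin 0.0325 (Sample size estimation); k = 10 facilities per arm (Study design).

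**Standard error of the difference**

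- Design effect = 1 + (m - 1) × 0.01 = 1 + 191 × 0.01 = 2.91
- SE = √[2 × p(1 - p) × 2.91 / (k × m)] = √[2 × 0.95 × 0.05 × 2.91 / 1920] = 0.0120
- Margin / SE = 0.0325 / 0.0120 = 2.708 (unrounded SE)

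**The plan's own figure (one-sided 5%, normal reference)**

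- Power = Φ(2.708 - 1.645) = Φ(1.064) = 85.6%, against 85% stated.
- Individually randomized n per arm for 85% = 2 × 0.95 × 0.05 × (1.645 + 1.036)² / 0.0325² = 646.6. Facilities needed at 192 each = 646.6 × 2.91 / 192 = 9.80, which rounds up to the planned 10.

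The stated design is thus reproduced at one-sided 5%.

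**The stated decision rule (one-sided 2.5%, normal reference)**

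- Power = Φ(2.708 - 1.960) = Φ(0.748) = 77.3%.
- Type II error = 100 - 77.3 = 22.7%, against the 15% implied by the text.
- For scale, 85% at this level needs n = 2 × 0.95 × 0.05 × (1.960 + 1.036)² / 0.0325² = 807.5 per arm before clustering. That is 807.5 × 2.91 / 192 = 12.24, so 13 facilities per arm at 192 each. With 10 facilities it is 807.5 × 0.99 / (10 - 8.075) = 415.4, so 416 per facility.

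**Where the two rules disagree, at the planned SE**

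- 90% interval: passes if the estimate exceeds -3.25 + 1.645 × 1.20 = -1.28 points.
- 95% interval: passes if the estimate exceeds -3.25 + 1.960 × 1.20 = -0.90 points.
- An estimate between -1.28 and -0.90 points passes one rule and fails the other. If the arms are truly equal, this happens with probability 85.6 - 77.3 = 8.3%.

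**Small-sample correction (assumption)**

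The article names neither the type of correction nor a reference distribution. If a t reference is used at one-sided 2.5%, the noncentral t distribution with noncentrality 2.708 gives:

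| Degrees of freedom | Power |
|---|---|
| 18 | 72.6% |
| 25 | 74.0% |
| 27 | 74.3% |

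**Stratum adjustment (assumption, in the other direction)**

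The article does not say whether 0.01 is the correlation before or after allowing for strata. If strata reduced it, power at one-sided 2.5% with a normal reference would be:

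| Effective correlation | Design effect | Power |
|---|---|---|
| 0.009 | 2.719 | 80.0% |
| 0.008 | 2.528 | 82.8% |
| 0.007 | 2.337 | 85.6% |

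Unequal facility sizes would lower these figures.

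**The case against.** The strongest defence is that the 95% interval was meant as a one-sided 95% bound, equivalent to the lower limit of a two-sided 90% interval. The levels would then agree and the 85% would stand. The text does not say so, and an unqualified 95% interval is normally read as two-sided. This reading changes which sentence needs correcting, but not the need to reconcile the two.

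A second defence is that the analysis rule is the stricter of the two. That is right. A reader might infer from two conflicting levels that type I error is inflated. It is not: a non-inferiority claim under the 95% interval rule remains valid, and only the planning statement is affected.

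A third objection is that a figure near 73% cannot be presented as the trial's real power. That also stands. It needs a t reference and degrees of freedom that the article does not give, and the same sentence that promises the variance correction also adds strata to the model, which could recover precision.

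A reader might go further in two directions that the document does not support. One is to quote the lower chance that both principal comparisons succeed together. The article judges each intervention separately and claims no joint power. Part of any such shortfall would also come from asking for two successes, not from the mismatch. The other is to conclude that larger enrolment is out of reach. Study monitoring allows sites to be expanded or replaced during accrual, although for balance, and Trial status describes recruitment as ongoing, so the document does not settle this.

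**Conclusion.** The inconsistency is real and is in the document as written. The sample-size arithmetic is right for a one-sided 5% test, but that is not the test in the decision rule. Under the 95% interval rule, power per comparison is about 77% instead of 85%, a loss of about 8 points that follows from the critical value alone.

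This rests on the two-sided reading of the interval and on the article's own assumptions: 95% retention in both arms, intracluster correlation 0.01, equal facility sizes and a normal reference. The range of about 73-74% depends on an assumed t reference with 18 to 27 degrees of freedom and should be quoted only with that label. The point should be fixed because it governs how an inconclusive primary result is read. It does not threaten the validity of a positive one.

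**What to change.** Keep the 95% interval rule and change one sentence in Sample size estimation, for example: *one-sided alpha 0.025; 192 participants per facility gives about 77% power per comparison (normal reference)*. If a figure allowing for the small-sample correction is added, state the reference distribution and degrees of freedom assumed.

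If one-sided 5% was the intention, change the decision rule instead to a 90% confidence interval, that is, a one-sided 95% bound. The trial is unblinded and had begun recruiting on 28 July 2017, so the deadline that matters is before any between-arm comparison of 12-month outcomes. That includes the interim analysis planned when half the participants have completed 12 months.

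Either way, the two sections should state the same level. Restating the power costs one sentence and a less favourable figure, and requires no change to enrolment.

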### Recruitment and enrollment procedures

Figure 2 illustrates the overview of time schedules for enrollment, interventions and assessments according to SPIRIT. During the enrollment period, study nurses will screen all patients arriving for ART-refill visits at the study facilities and patients in recently formed CARGs according to the eligibility criteria. Potentially eligible patients will be invited by the study nurses to participate in the study, and to receive viral-load testing. It is not mandatory for all patients in a CARG to participate in the study. Eligible patients at each site who provide informed consent and who have a viral load < 1000 copies/ml will be enrolled until the facility enrollment cap has been reached. All study participants at a particular facility will receive the same model of care based on the arm to which that facility has been allocated. Patients already in CARGs at facilities in the control arm at the commencement of the study will not be considered for recruitment, and they will continue to receive care in CARGs as per the national guidelines similar to those in the 3MC arm.

**Fig. 2 Fig2:**
[figure not shown]
Enrollment, interventions and assessment schedule according to Standard Protocol Items: Recommendations for Interventional Trials (SPIRIT)

### Participant follow-up

All participants will be followed up for 24 months. As retention in care is the primary outcome, there will be no involvement regarding defaulter tracking beyond which exists routinely at each facility. Viral-load testing will occur at annual intervals, according to national guidelines [18]. Participants who become pregnant, develop tuberculosis or other opportunistic infections, have unsuppressed viral loads (≥1000 copies/ml), or who become clinically unwell will require clinic follow-up visits more frequently than 3-monthly as per national guidelines, thus they will transition off the study arm. These participants will remain under observational follow-up for the remainder of the study period for ascertainment of the primary outcome. CARG participants will return to be followed up at the facility. Frequency of ART-dispensing and clinical management will then be determined based on clinician assessment and national guidelines.

As Zimbabwe is moving to have ART refills provided in CARGs as an additional option for stable ART patients at all facilities [18], participants in the 3MF arm will be consigned to receive ART 3-monthly supplied at the facility for 12 months after enrollment; thereafter, participants will be offered the option of forming CARGs that receive ART 3-monthly. Participants who decline to join CARGs will continue to be followed up as arm 3MF for a further 12 months. This design was chosen taking into account program implementation plans for PEPFAR partners as they prioritize the roll-out of CARGs. It will allow arm 3MF to have at least 12 months of follow-up time to analyze retention and virologic suppression. After 24 months, all participants will receive nationally applied standard of care as at the time of study completion.

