### Definitions

The primary outcome of retention in care will be defined as 1-participant attrition, where attrition is defined as either death (all-cause) or loss to follow-up (LTFU). LTFU will be defined as no facility or ART collection for > 90 days after the last missed scheduled ART collection [22, 23]. (Participants not arriving for the 12- or 24-month visit will be considered retained at these time points if collecting ART in person within 90 days of the scheduled appointment date). Participants with documented transfers to another clinic will be considered retained at the next immediate time point (12 or 24 months), and will then be censored. For the secondary outcome of retention in the study model of care, participants will be considered non-retained if transitioning off the study arm for any reason, including death, LTFU, change in ART-dispensing frequency, incident comorbidity requiring more frequent clinic visits, personal preference or withdrawal of consent to participate. Reasons for a change in ART-dispensing frequency include incident opportunistic infections, drug toxicity requiring closer monitoring, provider judgment based on change in clinical status or inadequate adherence, viral load > 1000 copies/ml, or pregnancy. Viral suppression will be defined as a viral load < 1000 copies/ml.

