### Participant eligibility criteria

Participant eligibility will be aligned to those for stable ART patients in routine settings in Zimbabwe [24], and are shown in Table 1.

**Table 1 Tab1:** Inclusion and exclusion criteria for study participants

Inclusion criteria	Exclusion criteria
18 years of age or older	ART toxicity or tolerability issues in the prior 6 months
Confirmed HIV-1 infection based on the Zimbabwe national HIV-testing algorithm	Treatment for an opportunistic infection in the prior month
Received standard first-line ART for 6 months or longer	Receiving alternative first-line or second-line ART regimen
Viral load < 1000 copies/ml at enrollment	Active or suspected opportunistic infection
Weight ≥ 35 kg	Active or suspected tuberculosis
Willing to join a CARG	Comorbidities requiring more frequent visits to the facility than that required by the model of care
Provide informed consent for inclusion in the study	Confirmed pregnancy
	Less than 18 months postpartum

*ART* antiretroviral treatment, *CARG* community antiretroviral treatment-refill group, *HIV* human immunodeficiency virus

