## Discussion

No large-scale trials have been conducted investigating patient-level outcomes and health system costs of extended ART-dispensing intervals for patients within community-based groups in sub-Saharan Africa. The rationale for this study is to provide evidence regarding the effectiveness and cost-effectiveness of extended dispensing intervals for ART patients within CARGs, and whether these are suitable strategies that can be implemented on a larger scale to help overburdened health facilities with the large numbers of patients and reduce the burden and cost to patients of frequent clinic visits. Study results are expected to inform health policy both in Zimbabwe and in the entire sub-Saharan African region.

The trial is implemented through a collaboration between Kheth’Impilo AIDS Free Living, EQUIP Innovation for Health, the Organization for Public Health Interventions and Development, FHI 360, the Zimbabwe AIDS Prevention Project Trust and the Zimbabwe MOHCC. Implementation challenges include large distances between facilities, limited access to routine viral-load testing within the country and limited Internet connectivity in rural areas.

The strengths of the study include that a variety of outcome data will be analyzed including clinical effectiveness data, provider- and patient-cost data, qualitative data and site-level impact data. Routine ART facilities from both urban and rural areas are included in a pragmatic design, which is expected to allow study results to be generalizable to other sub-Saharan African settings. The study limitations include that participants in the 3MF arm may not complete 24 months’ follow-up in this arm as, according to MOHCC operational recommendations, they will be provided the option of forming CARGs after 12 months of study participation. The sample size in the 3MF arm may thus be reduced at the 24 months’ outcomes assessment, thus comparisons may have reduced power. However, this will not impact the primary outcome ascertainment of patient retention 12 months after enrollment. Participant viral-loads results may not be complete due to limitations in the availability of viral-load testing in the country. Viral suppression is thus a secondary outcome. It will also not be possible for participants or providers to be blinded as to the study group allocation.

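### The protocol leaves open whether control participants who join CARGs after 12 months still count in 3MF at 24 months; either reading biases the 24-month comparisons with 3MF, yet only reduced power is named

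*Protocol article*

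**What the plan says.** - **Protocol article, Participant follow-up.** 3MF participants stay on facility refills for 12 months; "thereafter, participants will be offered the option of forming CARGs that receive ART 3-monthly". Then: "Participants who decline to join CARGs will continue to be followed up as arm 3MF for a further 12 months". The same section states that follow-up lasts 24 months for every participant.
- **Discussion, limitations.** "The sample size in the 3MF arm may thus be reduced at the 24 months’ outcomes assessment, thus comparisons may have reduced power". It adds that "this will not impact the primary outcome ascertainment of patient retention 12 months after enrollment".
- **Outcomes and hypotheses.** Every outcome is to be compared across the three arms. Retention in care, viral suppression, retention in the study model of care and costs per participant retained all have a 24-month assessment.
- **Quantitative patient-level data analysis.** "Individual-level outcome analyses will be conducted by intention-to-treat". For viral suppression this is spelled out as all enrolled participants, in their original arm.
- **Definitions.** For retention in the study model of care, "participants will be considered non-retained if transitioning off the study arm for any reason"; personal preference is among the listed reasons. No exception is made for the CARG offer.
- **Table 1.** An inclusion criterion for all participants is "Willing to join a CARG".

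**The concern.** Joining a CARG can shrink the 3MF sample at 24 months only if joiners leave the 3MF comparison. The Discussion therefore implies a control group of decliners. Intention-to-treat and 24-month follow-up of everyone imply the opposite: joiners stay and the sample does not fall for this reason. The protocol does not reconcile the two.

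The choice matters because each reading carries a bias, and a bias is not cured by a larger sample or a wider interval. Decliners are a group formed after randomisation, set against whole CARG arms. Since everyone enrolled had said they were willing to join a CARG, those who later decline may well be atypical. If everyone is kept, part of the control arm spends year 2 on the model it is being compared with. In a non-inferiority trial, shrinkage toward zero makes the favourable conclusion easier.

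The model-of-care outcome has its own problem: a switch that the protocol itself offers to the control arm is scored as failure, and the CARG arms receive no matching offer.

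**Working it through.** **Inputs from the Sample size estimation section:** retention 95% in each arm at 12 months, intracluster correlation 0.01, margin 3.25 points, 10 facilities per arm, 192 participants per facility, one-sided α 0.05, power 85%.

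**Assumptions (not in the document):** share j of 3MF joining CARGs 25%, 50% or 75%; the 12-month margin and 95% confidence-interval rule applied again at 24 months; 95% retention used for the variance unless stated.

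**1. The plan's own figure.** Unclustered n = 2 × 0.95 × 0.05 × (1.645 + 1.036)² / 0.0325² ≈ 647 per arm. Design effect = 1 + 191 × 0.01 = 2.91. 647 × 2.91 ≈ 1,883, against 1,920 stated (1.9% apart). At 1,920 per arm, SE = √(2 × 0.0475 × 2.91 / 1920) = 0.0120, and power = Φ(0.0325/0.0120 − 1.645) = 85.6%. The figure reproduces.

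**2. The power loss that the Discussion names.** With a share 1 − j of 3MF kept, SE² = 0.0475 × 2.91/1920 + 0.0475 × [1 + (192(1 − j) − 1) × 0.01] / [1920(1 − j)]. At j = 50% this gives SE = 0.0130. Power (one-sided 0.05) goes from 85.6% to 83.9%, 80.5% or 71.2% at j = 25%, 50% or 75%. If 24-month retention is 0.95² = 90.25%, it goes from 63.5% to 61.4%, 57.7% or 49.0%.

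**3. Reading A: decliners only.** Let g be the 24-month retention of joiners minus that of decliners, had both stayed on facility care. The decliners' mean lies j × g below the full-arm mean, so the risk difference (CARG minus 3MF) shifts by +j × g. The shift equals 3.25 points when g = 3.25/j. With a true difference exactly at −3.25 points, the chance of wrongly declaring non-inferiority is Φ(j × g/SE − 1.96):

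| j | g giving a 3.25-point shift | g = −2 | g = 0 | g = +2 | g = +5 |
|---|---|---|---|---|---|
| 25% | 13.0 | 0.9% | 2.5% | 6.0% | 17.2% |
| 50% | 6.5 | 0.3% | 2.5% | 11.7% | 48.6% |
| 75% | 4.33 | 0.1% | 2.5% | 17.3% | 72.0% |

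The sign of g is unknown. If decliners do better (g negative), true non-inferiority becomes harder to show.

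**4. Reading B: all 3MF kept as allocated.** Assume that half of a true −3.25-point 3MC–3MF difference arises in year 2 and that joiners then share the 3MC result. The observed difference is −3.25 × (1 − 0.5j) = −2.84, −2.44 or −2.03 points. The same formula, with SE 0.0120, gives false non-inferiority of 5.2%, 10.0% or 17.3%.

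**5. Sensitivity.** At 90.25% retention the SE grows by √(0.0880/0.0475) = 1.36. At j = 50%, 11.7% becomes Φ(0.010/0.01767 − 1.96) = 8.2%, 48.6% becomes Φ(0.025/0.01767 − 1.96) = 29.3%, and 10.0% becomes Φ(0.008125/0.01633 − 1.96) = 7.2%. The rates are smaller but still well above 2.5%.

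**6. Model-of-care retention, scored as written.** At 95% retention in care per year, the most that 3MF can reach at 24 months is 0.95² × (1 − j) = 0.9025 × 0.75, 0.50 or 0.25 = 68%, 45% or 23%. The CARG arms have a ceiling of 0.9025, about 90%. Both are ceilings, because pregnancy, raised viral load, comorbidity, preference and withdrawal also count as failure in every arm.

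**The case against.** The strongest defence is that no section defines a decliners-only analysis set. The sentence on decliners can be read as describing the care they continue to receive, and the explicit analysis statement is intention-to-treat. That stands. A reader might infer that the 24-month 3MF comparison is fixed as a selected remnant, or that only participants retained to 12 months enter it. The document supports neither. The smaller sample in the Discussion implies the first without specifying it, and nothing removes year-1 deaths or losses from the denominator.

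The defence does not clear the plan. If intention-to-treat governs, the Discussion is wrong about the sample shrinking, and crossover to the 3MC model takes the place of selection.

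It is also fair that selection and model-of-care failure require opposite handling of joiners. They are therefore alternatives, not additive harms: selection arises if joiners leave 3MF, and the model-of-care ceiling applies if they stay in its denominator, as the definition of failure presupposes.

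The offer and its programmatic reason are openly disclosed, and uptake is unknown. Detail on analysis sets may properly sit in an analysis plan that is not shown. The point here is narrower: two statements in the document conflict, and the consequence it names is incomplete.

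**Conclusion.** The point holds as an unreconciled conflict with a misdescribed consequence, and should be fixed. Reduced power is a real but lesser effect: at 50% joining and 95% retention, power falls by about 5 points (85.6% to 80.5%). Under the same conditions, a 2-point deficit in decliners raises false non-inferiority from 2.5% to 11.7%, and crossover with everyone kept raises it to 10.0%. Selection may act in either direction. The pull toward zero under crossover applies to 3MC versus 3MF; for 6MC versus 3MF, the control becomes partly 3MC and the direction depends on how those two models differ.

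The model-of-care distortion follows directly from the definition as written and grows with uptake.

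All sizes rest on assumed uptake, joiner–decliner gap, timing of effect and 24-month retention. A reader might infer that the trial's main conclusion is at risk. It is not: the 12-month primary outcome, other 12-month comparisons and 6MC versus 3MC are untouched, and the protocol is right to say so of the primary outcome.

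**What to change.** 1. State that 24-month outcomes include all 3MF participants as allocated, and label that arm *12 months facility, then choice of CARG*.
2. Treat any decliners-only analysis as descriptive.
3. Draw no 24-month non-inferiority conclusion about uninterrupted facility care versus CARGs. Name 6MC versus 3MC as the 24-month comparison of uninterrupted models. Step 1 removes selection but leaves crossover, so this step is needed as well.
4. Limit the model-of-care comparison with 3MF to 12 months, or do not count the protocol-offered switch as failure.
5. In the Discussion, replace "thus comparisons may have reduced power" with selection and crossover as the limitations.

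The CARG offer itself is not in question. The change is to analysis wording only, since everyone is already followed for 24 months. The cost is a narrower 24-month claim against 3MF. Settling it before 24-month data are seen also avoids choosing the analysis population with results in hand.

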### Outcomes and hypotheses

The rationale for the control arm selection is that provision of ART refills 3-monthly at the facility is the most established standard of care option for stable ART patients in Zimbabwe. All outcomes will be compared between all three arms. The primary outcome is participant retention in care, defined as the proportion of participants remaining in care 12 months after enrollment by intention-to-treat. Retention in HIV care is one of the most important determinants of the overall impact of ART [21]. Retention in care will also be compared after 24 months.

The principal hypotheses are that participant retention in both the intervention arms will be non-inferior to retention in the control arm with a non-inferiority margin of − 3.25% (risk difference). An additional hypothesis is that retention in intervention arm 6MC will be non-inferior to retention in intervention arm 3MC. The rationale for the non-inferiority design is that we anticipate retention to be at least similar in the intervention arms vs. control, and anticipate that provider (and participant-level) costs will be lower in the intervention arms vs. the control due to reduced participant contact with healthcare facilities in the intervention arms. If clinical outcomes in the intervention arms are at least non-inferior compared to the control arm, the interventions are anticipated to show cost savings compared to the control.

The secondary outcomes are:I.The proportion of participants achieving virological suppression 12 and 24 months after study enrollmentII.The proportion of participants retained in the study model of care after 12 and 24 monthsIII.Average annual cost per participant from a provider perspectiveIV.Average provider cost per participant retained, and average provider cost per participant retained with virological suppression 12 and 24 months after enrollmentV.Average annual participant-level expenditure to access treatmentVI. Qualitative research to assess the acceptability of multimonth dispensing (MMD) of ART within CARGs from both a participant and healthcare provider perspectiveVII. Site-level indicators of potential facility-level decongestion during the study. These are:Median difference in facility patient waiting times after 12 and 24 months compared to baselineTrend in the monthly number of patients newly initiated on ARTTrend in the monthly number of patients who receive provider-initiated HIV counseling and testing at the clinic

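### The follow-up and limitations text implies that 3MF participants who join a CARG at month 12 leave the 3MF arm at 24 months; this conflicts with the intention-to-treat rule and presents a risk of bias as lost power only

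*Protocol article*

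**What the plan says.** All statements are in the protocol article.

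- **Outcomes and hypotheses.** Retention is primary at 12 months, and "Retention in care will also be compared after 24 months". Viral suppression is a secondary outcome at 12 and 24 months. All outcomes are compared between all three arms.
- **Participant follow-up.** Everyone is followed for 24 months. 3MF participants receive facility refills for 12 months; "thereafter, participants will be offered the option of forming CARGs that receive ART 3-monthly". Then: "Participants who decline to join CARGs will continue to be followed up as arm 3MF for a further 12 months". The reason given for the design includes: "It will allow arm 3MF to have at least 12 months of follow-up time to analyze retention and virologic suppression".
- **Discussion, limitations.** Because of the CARG option, "The sample size in the 3MF arm may thus be reduced at the 24" months' assessment. Reduced power is the only consequence named. The text adds, correctly, that the 12-month primary outcome is untouched.
- **Quantitative patient-level data analysis.** "Individual-level outcome analyses will be conducted by intention-to-treat". For suppression the first analysis follows "an intention-to-treat principle including all enrolled participants in the arm to which they were originally allocated".
- **Participant eligibility criteria, Table 1.** One inclusion criterion is "Willing to join a CARG".

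**The concern.** Under intention-to-treat, a 3MF participant who joins a CARG after month 12 is still a 3MF participant at month 24, so CARG uptake cannot reduce the arm. The expected reduction makes sense only if joiners leave the 3MF analysis, and the follow-up section points the same way by carrying only decliners forward as 3MF.

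Dropping joiners would cost more than power. Only people alive and in care at month 12 can take up the offer. Removing them takes out people who have already succeeded for a year and leaves every first-year death and loss in the arm. A team following the limitations text would therefore compare two intact randomised arms with a selected remnant of the third.

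A team following the analysis section avoids that bias but meets a different limitation, which the article does not mention: in year 2 part of the control arm receives the 3MC model.

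**Working it through.** **1. The plan's own figure.** Inputs from Sample size estimation: 95% retention in both arms, margin 3.25 points, one-sided alpha 0.05, power 85%, ICC 0.01, 192 participants in each of 10 facilities per arm.

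- Individually randomised size: 2 × 0.95 × 0.05 × (1.645 + 1.036)² / 0.0325² = 647 per arm.
- Design effect: 1 + 191 × 0.01 = 2.91.
- Product: 647 × 2.91 = 1883 per arm, 1.9% below the stated 1920. Power at 192 per facility is 85.6%.

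The stated 1920 is reproduced and is the 3MF starting number below.

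**2. Assumptions for month 24.** The article gives neither second-year retention nor CARG uptake. I assume 95% retention in year 2 for everyone, with no difference between arms or between joiners and decliners. Let u be the share of 3MF participants in care at month 12 who join a CARG. True 24-month retention is then 0.95 × 0.95 = 90.25% in every arm.

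**3. Joiners removed, first-year losses kept.**

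Apparent 3MF retention = 0.9025(1 − u) / [0.05 + 0.95(1 − u)]; number left = 1920(1 − 0.95u).

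| u | Number left | Apparent 3MF retention | Error against 90.25% |
|---|---|---|---|
| 25% | 1464 | 0.6769 / 0.7625 = 88.8% | −1.5 points |
| 50% | 1008 | 0.4513 / 0.5250 = 86.0% | −4.3 points |
| 80% | 461 | 0.1805 / 0.2400 = 75.2% | −15.0 points |

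The error reaches 3.25 points when the expression equals 0.87. This gives 0.076(1 − u) = 0.0435, so u is about 43%. The error favours the CARG arms.

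**4. 3MF limited to decliners in care at month 12.** Apparent retention = 0.95(1 − u)(0.95) / [0.95(1 − u)] = 95.0% at any u. The error is +4.75 points and now favours 3MF.

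**5. Power loss, for scale.** Keeping 95% retention and one-sided 0.05 for illustration, shrinking 3MF to 1440, 960 or 480 lowers power from 85.6% to 83.9%, 80.5% or 71.2%.

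**6. All 3MF enrollees kept as allocated.** The denominator does not depend on u. Joiners receive 3-monthly CARG refills, so if they take on 3MC year-2 retention:

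- 3MC versus 3MF: a true year-2 difference is reduced to (1 − u) of its size, for example 20% at u = 80%.
- 6MC versus 3MF: write the year-2 difference as a CARG-versus-facility part plus a 6-versus-3-month part. Only the first is multiplied by (1 − u).
- Year-1 differences arise before the offer and are not diluted by it.

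**The case against.** The strongest reply is that no sentence excludes joiners. The follow-up section opens by keeping everyone for 24 months, and it explicitly keeps those who move off the arm for clinical reasons under observation for the primary outcome. Continuing as 3MF could simply mean staying on that model of care, which the Definitions treat as a separate outcome. The suppression analysis names its intention-to-treat set outright. The crossover is planned, justified by national roll-out, and disclosed.

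Much of this stands. Exclusion is an inference, and for suppression the analysis text already gives the right rule. But the reply does not explain why the 3MF sample size should fall because of the CARG option, nor why the design is said to secure only a minimum of 12 months of 3MF follow-up for retention and suppression.

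Four stronger readings are tempting and not supported:

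- *The bias will exceed the margin.* Uptake is unknown. Table 1 makes substantial uptake plausible, but the offer is optional and CARGs need 6–12 people from a similar location. At 25% uptake the error is 1.5 points, and its sign depends on how first-year losses are handled. The 3.25-point margin was sized for 12 months and is only a yardstick here.
- *Suppression at 24 months is biased by a known amount.* Nothing here quantifies that.
- *Intention-to-treat makes 24-month similarity near automatic.* Year-1 differences, and the dispensing-interval part of 6MC versus 3MF, are not diluted by the offer.
- *The power caveat should simply go, and 6MC versus 3MC should become the 24-month comparison.* Dilution does weaken the contrast with 3MF, and the article plans comparisons of all three arms.

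**Conclusion.** The conflict is real and confined to the 24-month comparisons with 3MF. The follow-up and limitations text implies that joiners leave the arm; the analysis section implies that they stay. On the stated assumptions, the choice moves apparent 24-month 3MF retention from 90.25% to between 88.8% and 75.2% (uptake 25% to 80%, first-year losses kept), or up to 95.0% (decliners in care at month 12 only), with no true difference between arms. Describing this as reduced power misses the main hazard, which is selection. These figures illustrate what would follow if joiners were dropped; they do not predict the trial's result. They rest on assumed uptake, assumed 95% second-year retention, and joiners and decliners being otherwise alike. The 12-month primary outcome and 6MC versus 3MC are not affected. This should be corrected, but it does not threaten the main conclusion.

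**What to change.** 1. In Participant follow-up and in the Discussion, state that all 3MF enrollees are followed and analysed in 3MF at 24 months for retention in care and viral suppression, whether or not they join a CARG. This is subject to the rule in Definitions that censors documented transfers after the next time point.
2. Label any analysis limited to decliners as supplementary.
3. Replace the reduced-sample-size statement with the actual limitation. At 24 months the contrast with 3MF is CARG from enrolment versus 12 months of facility care followed by a CARG option. This dilutes year-2 facility-versus-CARG differences: the whole year-2 difference is exposed for 3MC versus 3MF, but not the 6-versus-3-month component of 6MC versus 3MF.
4. Add that similarity with 3MF at 24 months should not be read as non-inferiority to continued facility care.

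The cost is wording in the protocol and, where it covers this point, the SAP. Follow-up to 24 months is already planned for everyone and no one's care changes. The price is a narrower 24-month claim against 3MF. Settling the rule before 24-month data are seen also removes the chance to choose between analyses that could differ by several points.
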